# Effects of vildagliptin compared with glibenclamide on glucose variability after a submaximal exercise test in patients with type 2 diabetes: study protocol for a randomized controlled trial, DIABEX VILDA

**DOI:** 10.1186/1745-6215-15-424

**Published:** 2014-11-04

**Keywords:** Diabetes mellitus, Hypoglycemic agents, Exercise

## Abstract

**Background:**

Cardiovascular disease, endothelial dysfunction, and oxidative stress are common complications among patients with type 2 diabetes (T2DM). In addition to the average blood glucose concentration, glycemic variability may be an important factor for the development of chronic diabetes complications. Patients with T2DM are treated with various types of oral glucose-lowering drugs. Exercise is considered to benefit the health of both healthy and unhealthy individuals, which has been confirmed by a number of scientific research studies in which the participants’ health improved. Our general aim in this study will be to evaluate glucose variability after submaximal exercise test in patients receiving treatment with either vildagliptin or glibenclamide. The specific aims of this study are to evaluate the oxidative stress, endothelial function, and metabolic and cardiovascular responses to exercise under treatment with vildagliptin or glibenclamide. All these responses are important in patients with T2DM.

**Methods/Design:**

This study is a PROBE (Prospective, Randomized, Open-label, Blinded-Endpoint) design clinical trial.

The estimated sample needed is 20 patients with T2DM. In addition to the routine treatment (metformin), patients will receive a second drug orally for 12 weeks: the METV group will receive metformin plus vildagliptin (50 mg twice daily), and the METG group will receive metformin plus glibenclamide (5 to 10 mg twice daily.). Before and after intervention, evaluation of glycemic variability, endothelial function, oxidative stress, and metabolic and cardiovascular response will be performed at rest, during and after a submaximal exercise test (30 minutes, with an intensity based at 10% under the heart rate at the second threshold).

**Discussion:**

In addition to drug treatment, exercise is recommended for treatment of glycemic control in patients with T2DM, especially for its beneficial effects on blood glucose and HbA1c. Few studies have determined the effects of the association between exercise and oral glucose-lowering drugs. The study will be conducted to assess the metabolic and cardiovascular responses at rest, and during and after submaximal exercise in patients receiving one of two oral glucose-lowering drugs (vildagliptin or glibenclamide).

**Trial registration:**

ClinicalTrials.gov Identifier: NCT01867502 study release date: May-17-2013.

## Background

Cardiovascular disease is the main cause of mortality among people with type 2 diabetes mellitus (T2DM) [1, 2]. Accelerated atherosclerosis in these patients is preceded by endothelial dysfunction, inflammatory burden, and increased lipid peroxidation, all leading to enhanced macrophage foam cell formation [2]. In addition to the average blood glucose concentration, acute glycemic fluctuations from peaks to nadirs (glucose variability) may be involved in the development of diabetic complications [3], as they contribute to the generation of excessive protein glycation and oxidative stress [4]. High glucose variability has been shown to be associated with endothelial dysfunction in patients with T2DM and optimal metabolic control [5]. Currently, the mean amplitude of glycemic excursion (MAGE) is one of the most used methods for detecting significant swings in glycemia [6], but other tools may be useful to identify disturbances in glucose variability [7].

Some current treatments for T2DM have already been tested concerning their possible effects in reducing glucose variability as well as reducing glycated hemoglobin (HbA1c) [8]. Exercise, which is one of the cornerstones of treatment for hyperglycemia in T2DM because of its beneficial effect on HbA1c [9], was recently shown to reduce glucose variability in addition to its acute effects on reducing glucose levels [7]. Vildagliptin and sitagliptin are two drugs that were recently evaluated in a study focusing on possible differences in daily glucose fluctuations in patients with T2DM inadequately controlled with metformin, and it showed that vildagliptin was more effective in flattening acute glucose fluctuations over a day [8]. Moreover, acarbose was superior to glibenclamide in reducing MAGE. Therefore, aside from their absolute glucose-lowering effect, it is evident that other effects of different anti-diabetic agents might also be different [10].

The present study will be conducted to test the hypothesis that in combination with metformin, vildagliptin may produce a greater improvement in glucose variability after a submaximal exercise test, compared with glibenclamide. Our general aim will be to evaluate glucose variability after the submaximal exercise test in patients receiving treatment with vildagliptin or glibenclamide. The specific aims of this study are to evaluate the oxidative stress, endothelial function, and metabolic and cardiovascular responses to exercise in patients treated with vildagliptin or glibenclamide.

## Methods/Design

### Research design

This study is a PROBE (Prospective, Randomized, Open-label, Blinded-Endpoint) design clinical trial.

### Outcomes

The primary outcome will be glucose variability evaluation, as evaluated by conventional and non-conventional methods. Secondary outcomes will include oxidative stress, endothelial function, and metabolic and cardiovascular responses to exercise. Table 1 shows the measures that will be evaluate to reach the outcomes.

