### Glucose variability evaluation

CGMS will be utilized for this evaluation. Subjects will be admitted to the laboratory in the morning at approximately 08.00 hours, 24 hours before the exercise session, when the glucose sensor (Sof-SensorTM; Medtronic Mini-Med Inc., Northridge, CA, USA) will be inserted subcutaneously. The sensor is a glucose oxidase-based platinum electrode that is inserted through a needle into the subcutaneous tissue of the anterior abdominal wall, using a spring-loaded device (Senserter, Medtronic Mini-Med Inc.).

Glucose oxidase catalyzes the oxidation of glucose in the interstitial fluid, which generates an electrical current. The current is carried by a cable to a pager-sized monitor that analyzes the data every 10 seconds and reports average values every 5 minutes, to give a total of 288 readings per day. Glucose profiles will be collected on the day before (day 1), the day of (day 2), and the day after (day 3) the submaximal exercise test. Sensor readings will be calibrated with a glucose monitor (Accu-Check Performa; Roche Diagnostics) using four finger-stick blood samples for each 24 hours. Each sensor will be used continuously for up to 48 hours. All patients will have been instructed previously about the operation of the monitor, which includes event registration for meals, and inserting capillary glucose values for calibration.

Glucose variability will be assessed from a series of absolute values of glucose, obtained by the CGMS, sampled every 5 minutes. Each method will be used as reported in the literature and according to its limitations. Glucose variability will be evaluated using conventional analysis and other mathematical methods generally applied to biological series, here called “non-conventional analysis of glucose variability.” Conventional analysis of glucose variability will be constructed from the statistical properties of the series, to obtain the following indices: MAGE [6], glucose variance (VAR), glucose coefficient of variation (CV%), and glucose SD, all normalized by the mean blood glucose in each period [15, 16]. These indices, except MAGE, will be calculated for every 6 hour block of glucose values to obtain the measures according to the specific period of the day. The MAGE index will be calculated for the whole signal (24 hours), and its calculation is based on the differences between consecutive points, considering those which are higher than 1SD [16].

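### The primary outcome is a family of glucose-variability indices with no lead index, and the one index used for sample size (MAGE) has no window tied to the post-exercise period

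*Protocol article*

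**What the plan says.** The Outcomes section defines the primary outcome in one sentence: "The primary outcome will be glucose variability evaluation, as evaluated by conventional and non-conventional methods". The section on glucose variability evaluation then says what this covers.

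- **Conventional indices:** "MAGE [6], glucose variance (VAR), glucose coefficient of variation (CV%), and glucose SD", all normalized by mean glucose in the period concerned. On timing: "These indices, except MAGE, will be calculated for every 6 hour block of glucose values".
- **Non-conventional methods:** spectral analysis, and symbolic analysis yielding Shannon entropy and four pattern categories.
- **MAGE window:** "The MAGE index will be calculated for the whole signal (24 hours".
- **Recording:** the sensor is inserted "24 hours before the exercise session, when the glucose sensor" is used, and "Each sensor will be used continuously for up to 48 hours".

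The hypothesis in the Background is that, added to metformin, "vildagliptin may produce a greater improvement in glucose variability after a submaximal exercise test, compared with glibenclamide". The Sample size calculation section uses MAGE only, in mg/dl, at week 12. The Statistical analysis plan section lists t-tests and repeated-measures ANOVA and gives one significance level, P < 0.01, without ranking the indices.

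**The concern.** A confirmatory trial needs one stated quantity on which its main claim stands or falls, or a rule for combining several. Here the primary outcome is a concept measured in many ways. One index is used for the sample size, yet nothing gives it precedence in the analysis. If the arms differ on one index and not on the others, the article does not say whether the hypothesis is supported, and the stated 1% level does not describe the chance of a false primary claim.

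The index behind the sample size is also loosely specified. The hypothesis concerns variability after exercise, but the 24 hours over which MAGE is taken are not identified, and the recording contains a full day before exercise. The scale differs too: mg/dl in the sample size, normalized in the analysis. Two analysts following the article could compute different primary results from the same sensor data.

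**Working it through.** **1. The plan's own figure.** Inputs from the Sample size calculation section: difference 25 mg/dl and SD 16 mg/dl (my reading of the stated mean ± SD), two-sided 1%, power 90%, two-sample t-test, 10% dropout, 20 in total. Equal allocation is assumed.

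Normal approximation, per arm: 2 × (2.576 + 1.282)² × 16² / 25² = 2 × 14.88 × 0.4096 = 12.2, so 13. Total 26 / 0.9 = 28.9, so 29. The exact t calculation needs 14 per arm: 28 / 0.9 = 31.1, so 32. The stated 20 is not reproduced. With 18 evaluable patients (9 per arm) the exact power at 1% is about 65%. That is a separate error. It matters here only because MAGE is the one index with a sample size calculation, and it does not reach the stated power.

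**2. Number of primary measures for the post-exercise day.** A 24-hour day has four 6-hour blocks. The article does not say how many spectral outputs there are, so one is assumed.

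- No merging: MAGE 1 + (VAR, CV%, SD) 3 × 4 + symbolic 5 + spectral 1 = 19.
- SD divided by the mean is CV%, so SD drops out; the four pattern categories are treated as shares of a whole, so one drops out: 1 + 2 × 4 + 4 + 1 = 14.
- Normalized VAR, CV% and SD counted as one index per block: 1 + 4 + 5 + 1 = 11.
- As the last, with one model covering the four blocks: 1 + 1 + 5 + 1 = 8.

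**3. Chance of at least one false positive at 1% each.** Under independence it is 1 − 0.99^k. For correlated measures I simulated 100,000 trials per cell, with 9 per arm, two-sample t-tests and a common correlation between all measures.

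| k | independent | correlation 0.5 | correlation 0.8 |
|---|---|---|---|
| 8 | 7.7% | 6.6% | 4.1% |
| 11 | 10.5% | 8.3% | 5.1% |
| 14 | 13.1% | 9.8% | 5.7% |
| 19 | 17.4% | 12.3% | 6.5% |

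Every cell is at least four times the stated 1%.

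**4. The MAGE window.** Insertion is 24 hours before exercise and use is at most 48 hours, so the recording splits into 24 hours before and at most 48 − 24 = 24 hours from the start of exercise. The whole signal is therefore up to 48 hours, not 24. If it means one 24-hour part, the text does not say which. The Sample size calculation section adds only that the time point is week 12.

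**5. The MAGE scale.** The sample size uses mg/dl. The evaluation section normalizes all four conventional indices, MAGE included, by mean glucose. The assumed difference of 25 and SD of 16 mg/dl do not carry over to the normalized index without further information.

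**The case against.** The strongest reply is that the article never says that one significant index makes the trial positive. It gives one general level and says that indices are calculated per block, not that each block is tested. The repeated-measures ANOVA might handle all blocks in one model. An analysis plan not shown here might rank or adjust the indices. Many of the measures nearly duplicate one another, so a raw count overstates the problem. The 1% level also gives some protection: five independent tests at 1% give 1 − 0.99^5 = 4.9%.

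Much of this stands, and it rules out some stronger readings that a reader might infer.

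- That any index in any block below 0.01 is by rule a positive trial. No such rule is written. The error rates above are conditional on that use.
- That the family is 38 tests (2 × 19, both sensor days), with a 32% false-positive chance. This counts the pre-exercise day, although the stated aim concerns the period after exercise.
- That the plan intends to confirm its hypothesis from pre-exercise data. The Background states the aim clearly and Table 1 lists variability separately at rest, during and after exercise. The wording leaves the window open; it does not direct the analyst to the wrong one.
- That post-exercise MAGE is invalid because it cannot separate an exercise response from a drug effect already present at rest. The hypothesis asks only which drug gives the greater improvement after exercise, so that separation is a further question.

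What the reply does not answer is that the choice of primary endpoint, its window and its scale belong in the protocol. The article does state them, and states them inconsistently. Nor does it present the 1% level as an allowance for multiple indices.

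**Conclusion.** The point holds in this form: the primary outcome has no lead index, while the sample size rests on one index whose window and scale do not agree across sections. If any significant index were taken as success, the chance of a false positive would be about 8% to 17% for 8 to 19 independent measures and about 4% to 12% at correlations of 0.8 to 0.5, against a nominal 1%. These figures assume one spectral output, the block handling shown for each count, equal arms of 9 and a common correlation. The article gives none of the correlations. The defects in window and scale rest on no assumption; they follow from setting the sections side by side. The remedy is a change of specification and does not question the measurements themselves.

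**What to change.** In the Outcomes section, name one primary endpoint: MAGE in mg/dl at week 12, over the recording from the start of the Day 2 submaximal test to sensor removal, up to 24 hours. Compare the arms with adjustment for the same measure at baseline, at the two-sided 1% level. In the section on glucose variability evaluation, replace the whole-signal wording with this window and state that normalization by mean glucose does not apply to this endpoint. The phrase up to 24 hours is needed because the 48-hour sensor limit leaves no slack. In the Statistical analysis plan section, name the baseline-adjusted comparison as the primary analysis and make all other indices, blocks and methods secondary or exploratory.

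Exercise-day minus rest-day MAGE, compared between arms, may be added as a secondary analysis. It uses data already recorded, but the hypothesis does not require it.

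The cost is protocol and registry wording, with no new visits or devices. The Trial status section describes the trial as not yet recruiting; the choice should be fixed before outcome data exist. The downside is that the other indices, including the non-conventional ones, lose primary status. Keeping all of them primary would cost more: with Bonferroni over 19 measures (0.01 / 19 = 0.00053 each) and the MAGE effect size assumed for every index, the exact t calculation needs 22 per arm, or 44 / 0.9 = 48.9, so 49 in total.

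Naming one endpoint does not restore 90% power at 1% with 20 patients. That shortfall needs its own correction.

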**Table 1 Tab1:** **Measures evaluated in order to reach the outcomes**

Time point	Data collection	Measure	Outcomes
At rest	Continuous glucose monitoring system	Glucose values	Glucose variability
	Vascular Doppler ultrasound	Flow-mediated dilatation	Endothelial function
	Blood sampling	Glucagon, glucose, HbA1c, insulin and GLP-1	Metabolic responses
	Impedance cardiography and electrocardiogram	Cardiac output, heart rate	Cardiovascular response
	24 hour urine	F2 isoprostane 8-isoprostaglandin F2α/ creatinine	Oxidative stress
During submaximal exercise tests	Continuous glucose monitoring system	Glucose values	Glucose variability
	Impedance cardiography and electrocardiogram	^a^Cardiac output, heart rate	Cardiovascular response to exercise
	Blood sampling	^a^Glucagon, glucose, insulin, and GLP-1	Metabolic responses
After submaximal exercise tests	Continuous glucose monitoring system	Glucose values	Glucose variability
	Impedance cardiography and electrocardiogram	^ab^Cardiac output, heart rate	Cardiovascular response to exercise
	Ambulatory blood pressure monitoring	24 hour blood pressure variability	
	Blood sampling	^ab^Glucagon, glucose, insulin and GLP-1	Metabolic responses

GLP-1, glucagon-like peptide 1; HbA1c, glycated hemoglobin. ^a^0, 15, and 30 minutes; ^ab^60 minutes after exercise.

### Sample size calculation

According to data reported by Marfella *et al*. [8], a total sample size of 20 patients (allowing for a dropout rate of 10%) should allow detection of a difference between groups with MAGE levels (mean ± SD) of 25.0 ± 16 mg/dl at week 12, assuming statistical power of 90%, and a significance level of 1% (two-sided, two-sample *t*-test).

### Inclusion and exclusion criteria

The inclusion criteria will be age older than 18 years, presence of T2DM, use of metformin, recent HbA1c between 7.5% and 10%, and no involvement in regular physical activity.

The exclusion criteria will be: current smoking; body mass index (BMI) >40 kg/m^2^; presence of proliferative diabetic retinopathy, ischemic heart disease, peripheral vascular disease, cognitive decline or dementia, neurological events, severe depression, or current diagnosed cancer; lactose intolerance; hepatic enzyme levels threefold higher than the reference values; glomerular filtration rate lower than 60 ml/min; blood pressure (BP) over 180/100 mmHg at rest; use of analgesic or anti-inflammatory drugs during the week of the study; use of insulin; and untreated thyroid dysfunction.

### Eligibility assessment and follow-up visits

Eligibility and exclusion criteria will take place in two visits, and will be assessed by medical records, patient interviews and laboratory tests.

A physician will be responsible for the cardiovascular assessment, using the American Heart Association guidelines [11]. The same physician will assess the presence of peripheral vascular disease using the ankle brachial index [12].

Two follow-up consultations will take place after 4 and 8 weeks of treatment to measure BP, heart rate, and body weight.

### Randomization

The randomization sequence will be generated by the R software (v2.12.1 Vienna, Austria, 2011), with a block size of five. Randomization to the metformin plus vildagliptin group (METV) or the metformin plus glibenclamide group (METG) will be performed by a researcher responsible only for this task, who will not participate in the recruitment, assessment, or intervention phases of the study.

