### Data collection

Eligible patients will initially perform a maximum effort test, and 48 hours later, they will begin the study protocol, as follows:

Day 1: Begin 24-hour urinary collection, perform vascular Doppler ultrasound to evaluate endothelial function, and then insert glucose sensor subcutaneously to begin continuous glucose monitoring system (CGMS) evaluation.Day 2: End the 24-hour urinary collection, carry out the submaximal exercise test (with blood collection at baseline, 15, and 30 minutes into the session, and 60 minutes after recovery). Assess heart rate variability 10 minutes before and after the submaximal exercise test, and begin 24 h ambulatory blood pressure monitoring (ABPM).Day 3: Removal of the glucose sensor; end 24 h ABPM. Randomization.

This same protocol will be repeated at the end of the 12-week treatment with vildagliptin or glibenclamide.

The experimental sessions will occur at the Exercise Pathophysiology Research Laboratory, Hospital de Clínicas de Porto Alegre (LaFiEx-HCPA), maintaining the ambient temperature at between 20 and 22°C.Patients will be asked to follow their habitual diet during the 3 days of protocol. To carry out the submaximal exercise test they will go to LaFiEx-HCPA in a fasted state. Patients will record detailed food intake in diaries across the 3 days of CGMS use. The dietary assessment will be performed using the software DietWin (DietWin, Porto Alegre, Brazil). In addition, participants will be instructed to avoid intense activities and not to consume caffeinated beverages on the day before the dietary assessment, in order to exclude any residual effect before and after the effort test. The submaximal exercise test will occur after a standard breakfast (500 kcal; 60% carbohydrate, 30% fat and 10% protein). During the drug treatment period (12 weeks) patients will not follow any kind of physical exercise program. The flow diagram of the study design is shown in Figure 1.

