### Study intervention

The METV group will receive 50 mg of vildagliptin orally twice a day. The METG group will receive glibenclamide 5 mg orally once per day during the first week of the study, then in the second week, the dose will be increased to 10 mg a day (5 mg twice a day). The dose may be adjusted to reach a target pre-prandial capillary plasma glucose level of 70 to 130 mg/dl without frequent or severe hypoglycemia, up to the maximum dose allowed (20 mg a day). Patients will be instructed to measure capillary glycemia using a glucose monitor (Accu-Check Performa; Roche Diagnostics, Mannheim, Germany) twice a week and at any time if they believe they have symptoms of hypoglycemia. These measured values will be recorded at the follow-up visits or passed on to the researchers in a phone call when two consecutive values lower than 70 mg/dl occur. This procedure will be explained at the beginning of the study. Medication adjustments will be guided by the researcher coordinator ([name]). Drug accountability will be assessed at each follow-up visit.

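### One constant block size of five in an open-label, single-laboratory trial of 20 lets staff who track past assignments know an expected 10% to 30% of later ones with certainty

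*Protocol article*

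**What the plan says.** The Randomization section names a single block size and describes no variation in it: "The randomization sequence will be generated by the R software (v2.12.1 Vienna, Austria, 2011), with a block size of five". There are two arms, and neither the allocation ratio nor the split within a block is given. Assignment "will be performed by a researcher responsible only for this task, who will not participate in the recruitment, assessment, or intervention phases of the study".

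Four other statements bear on the point:

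- Research design: "This study is a PROBE (Prospective, Randomized, Open-label, Blinded-Endpoint) design clinical trial". Treatment is therefore known to those who give it.
- Study intervention: "Medication adjustments will be guided by the researcher coordinator". At least one member of the study staff must know each patient's arm.
- Data collection: "The experimental sessions will occur at the Exercise Pathophysiology Research Laboratory", so there is one place where assignments accumulate. Randomization comes on Day 3, after the baseline tests.
- Sample size calculation and Trial status: 20 patients in total, with 16 months of data collection.

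**The concern.** A separate list holder keeps the list out of sight, but in an open-label trial past assignments can be seen by those who treat the patients. If the block length is constant and known, those assignments show where the current block stands and what remains in it. Some later assignments can then be deduced without access to the list.

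What is exposed is the decision whether and when to bring a patient in. Most eligibility criteria are numeric or documented, but a few need judgement (severe depression, cognitive decline, what counts as a recent HbA1c), and the timing of entry is free. Someone who expects a particular arm next could delay or screen out a patient thought unsuited to it. That would be selection bias. Blinded endpoint assessment would not remove it, because it arises before any endpoint is measured.

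This is a separate matter from five being odd. A constant block of four would balance the arms and still be predictable.

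**Working it through.** **Inputs.** Block size 5, two arms, N = 20, hence 20/5 = 4 blocks (Randomization; Sample size calculation). The split is not stated. Five cannot be divided equally between two arms, so I take each block as 3:2 or 2:3. I also assume that the observer knows the block size and the order of past assignments. The article gives no predictability figure to reproduce.

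An assignment is certain when the earlier ones in its block leave only one possible arm. The best guess is the likelier arm given what has been seen.

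**Reading A: every block 3:2 in the same, known direction.** There are 10 equally likely orders.

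- Positions 1 and 2: never certain.
- Position 3: certain if the first two are both the minority arm, (2/5)(1/4) = 1/10.
- Position 4: certain if the first three contain both minority places (3/10) or all three majority places (1/10), together 2/5.
- Position 5: always certain.

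Expected share: (0 + 0 + 1/10 + 2/5 + 1)/5 = 1.5/5 = 30%, or 6 of 20. Best guess: (3/5 + 3/5 + 7/10 + 7/10 + 1)/5 = 3.6/5 = 72%.

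**Reading B: the majority arm drawn at random for each block.** There are 20 equally likely orders.

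- Positions 1 to 3: never certain.
- Position 4: certain only if the first three are the same arm, 2/20 = 1/10.
- Position 5: certain if the first four stand at 3:1, 8/20 = 2/5.

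Expected share: (1/10 + 2/5)/5 = 0.5/5 = 10%, or 2 of 20. Best guess: (1/2 + 3/5 + 3/5 + 7/10 + 7/10)/5 = 3.1/5 = 62%.

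**Between the two.** If the direction is constant but learned only from the first block, that block behaves as in B and the other three as in A: (0.5 + 3 × 1.5)/20 = 5/20 = 25%.

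**Comparators.** For a constant block of 4, the chances of certainty by position are 0, 0, 1/3 and 1, so the share is (4/3)/4 = 33.3%. A single 10:10 list was solved by exact recursion. Random blocks of 4, 6 and 8 were simulated with an observer who knows the set of sizes and guesses optimally. Runs of 4,000 and 10,000 lists of 20 gave 2.5% and 2.3% certain.

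| Scheme | Certain in advance | Of 20 | Best guess right |
|---|---|---|---|
| Five, same known 3:2 | 30% | 6 | 72% |
| Five, direction random per block | 10% | 2 | 62% |
| Constant four | 33% | 6.7 | 71% |
| Single 10:10 list | 9% | 1.8 | 62% |
| Random 4, 6, 8 | about 2.5% | 0.5 | 67% |

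These are expected shares. In one block under reading A, up to 3 of 5 assignments can be certain.

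**Arm totals under blocks of five.** Reading A ends at 12:8. Reading B ends at 10:10 only if two of the four blocks favour each arm: 6/16 = 37.5%.

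**The case against.** Much of the case on the other side is fair.

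*The 30% is a worst case.* This stands. A reader might take 30% as the size of the problem, but it needs the same split in every block and staff who know its direction from the start, and the article states neither. It also implies 12:8, so it cannot be combined with an argument from 10 patients per arm. The 10% of reading B is close to the 9% left by a single 10:10 list.

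*The alternative does not beat blocks of five on every measure.* This stands too. Random 4, 6 and 8 blocks give a best guess of 67%, better than 72% but worse than 62%. Over 20 patients that is 13.4 expected correct guesses against 12.4 under reading B. Concealing the sizes does not change this: guessing the arm that is behind also succeeds about 67% of the time. What falls under either reading is the number of certain assignments.

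*Staff knowledge is assumed.* This stands in part. No passage says that recruiters follow the order of assignments, or that the coordinator who adjusts medication also recruits. The article is dated November 2014 and enrolment was planned from April 2014, so publication is not the main route by which the block size would become known. Patients overlapping between screening and Day 3 would lower every figure. Against that, 20 patients in one laboratory over 16 months make the sequence easy to follow.

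*Room for steering is small, and baseline imbalance would show.* Two eligibility visits, a maximal test and a 48-hour gap come before the test days, and glucose monitoring is recorded before randomization. A shift in baseline MAGE would be visible. A shift in unmeasured traits would not.

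*The details belong to the full protocol.* This does not stand. The article states one constant block size, which is a design choice and not an omission.

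**Conclusion.** The point holds as a range: an expected 10% to 30% of assignments (2 to 6 of 20) could be known in advance with certainty, depending on a split that the article does not state. It rests on staff knowing the block size and the order of past assignments.

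The separate list holder and Day 3 randomization are real safeguards for the list and for the baseline measurements. They do not reach the earlier decision about whom to bring in and when.

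A reader might go further and infer that enrolment will be steered or the MAGE comparison biased. The document does not support that: it shows that steering is possible, and no effect on MAGE can be calculated from it. This is a weakness worth correcting because correction is cheap, not a defect that invalidates the design.

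**What to change.** In the Randomization section, replace the constant block size of five with randomly varying even block sizes, for example 4, 6 and 8 in random order. Generate them in the same R script, and let only the researcher who holds the list know them. Keep the separate list holder and Day 3 randomization as they are.

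Certain assignments fall to about 2.5%, even for someone who knows the set of sizes. Every completed block is balanced, which also removes the imbalance built into blocks of five.

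The cost is one line of code and one sentence of protocol, with no new staff or system. Two downsides should be stated. If enrolment ends mid-block, the final split may miss 10:10 by a few patients; the extreme is 12:8, when a block of eight is cut after four patients in the same arm (8 + 4 against 8). And the average best guess stays near 67%, so the change removes certain knowledge of the next assignment, not every advantage in guessing it.
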